### **2.2.3. Implementation**

Randomization will be done using [www.randomization.com](http://www.randomization.com) by an independent person who will not participate in the implementation of the study. Study participants will be recruited from the 14 UNTAs (due to 7 per ZS) selected and upon admission each will receive a unique identifier corresponding to their group in the study. The IT will receive special training to enable it to know how to randomly assign the identifier to UNTA participants.

### **2.2.4. Blinding (masking)**

The statistician who will do the randomization will send the results in closed envelopes which will only be opened by the ITs of each selected UNTA. Neither the nurses who will take the anthropometric measurements nor the researchers will know which group each child

participating in the study belongs to. Due to the differing amounts of total RUTF sachets distributed, parents may deduct the dose their children will receive and thus not be blinded.

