### c. Strategies to improve protocol adherence

Every evening, the principal investigator, the ACF Research RP and the three data collectors check all the data collected in the field in the different UNTAs. Inconsistencies, outliers or missing information for certain variables are noted and communicated to ACF supervisors who follow up within 24 hours and strengthen the capacities of UNTA agents, and also to RECOs. During their visit to enter data, data entry clerks also communicate certain weaknesses observed to healthcare providers with a view to correcting the data as far as possible.

In some cases where trained providers have moved or left their posts, other providers will be trained by the research team to ensure the continuity of the study.

For each child who does not respond to an appointment, RECO makes a home visit to find out what is going on.

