### **2.2.2. Randomization concealment mechanisms**

Once the randomization lists are generated, they will be printed and kept in two copies, one at the ACF headquarters in Paris and the other at the ESP in Kinshasa. The randomization list for each UNTA will be sent by sealed envelope to the nurse in charge of the corresponding health area (IT). Researchers will not have access to the footage. Only ITs will have access to the randomization sequences of the corresponding UNTA.

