### b. Data collection plan

| Frequency of data collection                   | Admission | Weekly treatment max 12 weeks | Dump | Monthly follow-up +3 months after discharge | Monthly follow-up at +6 months after discharge |
|------------------------------------------------|-----------|-------------------------------|------|---------------------------------------------|------------------------------------------------|
| Selection for inclusion in the study           | X         |                               |      |                                             |                                                |
| Information, consent and randomization         | X         |                               |      |                                             |                                                |
| Sociodemographic questionnaire                 | X         |                               |      |                                             |                                                |
| Physical examination                           | X         | X                             | X    |                                             |                                                |
| Anthropometric measurements                    | X         | X                             | X    | X                                           | X                                              |
| Distribution of RUTF                           | X         | X                             |      |                                             |                                                |
| Psychomotor Development Score (DPM) Assessment | X         |                               | X    |                                             | X                                              |
| Individual interview for acceptability study   |           |                               |      |                                             |                                                |
| FGD                                            |           |                               |      |                                             |                                                |

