### **The principal investigator**

- Write the protocol, design the questionnaires, with the co-investigators
- Trains teams, partners, agents, service providers in the study protocol, its tools, and quality control
- Ensures coordination between everyone and project communication with the support of ACF
- Ensures quality control at the start of the study then during the study, being present on site, sets up the monitoring of data entry, the correction if necessary, the locking up of consents, the protection of data, mutual accountability of all to obtain reliable data
- Organizes coordination meetings in Mbuji Mayi between ACF, the owners of health centers and / or their representatives for the proper implementation of care and concomitant research
- Prepare monthly reports and presentations of study progress to inform study partners and decision makers
- Conducts the final statistical analyzes from the data, writes scientific articles presenting the results obtained with the partners, formulates the conclusions, and suggests operational recommendations for the PCIMA.
- Contributes to the drafting of proposals to secure additional funding
- Presents the final results to the authorities and representatives of the participants, to the international nutrition community and to the scientific community in the field.

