### **2.3.2. Data management**

The data will be collected on individual UNTA files by the IT then by double entry for 10% of the files, they will be recorded on tablets by the data entry officers recruited for the study. The principal investigator will regularly analyze the data collected after it has been sent to the central server and will provide feedback to the data collectors on the inconsistencies observed.

The principal investigator, the data entry agents under the supervision of the scientific manager, will have to check the quality of the data on a daily basis and provide feedback to the ACF supervisors and IT via the Research Program Manager for any corrections on the site.

Only the principal investigator and the Research Program Manager will have free access to the data during the study. The latter two are responsible for extracting the database from the server, making it anonymous and sharing it for statistical analysis.

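### The protocol states that researchers are blind to group, but its identifier scheme and its check, clean and analyse chain do not protect that, so the primary outcome may be handled with the arm known

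*Protocol*

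**What the plan says.** **Blinding.** Section 2.2.4 says of the measuring staff and the research team: "Neither the nurses who will take the anthropometric measurements nor the researchers will know which group each child" belongs to. Section 2.2.2 supports this: "Researchers will not have access to the footage" (the last word is evidently a mistranslation of sequences). The same section says of the lists that "they will be printed and kept in two copies, one at the ACF headquarters in Paris and the other at the ESP in Kinshasa".

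**Identifier.** Section 2.2.3 says "upon admission each will receive a unique identifier corresponding to their group in the study". Section 2.3.1 f adds that the provider who hands out the RUTF knows from the child's ID who is on the reduced dose. It also says that the group itself is not mentioned.

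**Weekly items.** The table in section 2.3.1 b has a row "Distribution of RUTF", marked at admission and at the weekly visits. Chart 5 in section 2.1.3 e has RUTF consumption assessed every week.

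**Who handles the data.** Section 2.1.3 c: "Every evening, the principal investigator, the ACF Research RP and the three data collectors check all the data collected in the field". Section 2.3.2: "The principal investigator will regularly analyze the data collected after it has been sent to the central server". Sections 2.3.2 and 3.7 limit raw-data access during the study to the principal investigator and the research program manager, and section 3.5 makes the same two responsible for cleaning the database in order to anonymise it. Data entry clerks may not act on the data without the researcher's agreement. The principal investigator's duties include: "Conducts the final statistical analyzes from the data".

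**The concern.** The blinding statement covers the researchers, yet the two people with the most influence over the data have possible routes to the arm, and the protocol describes nothing that closes them. It names no masked data view, no identifier free of group meaning and no analyst blind to the arm.

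The outcome leaves room for judgement. Section 2.3.1 a has each weight measured once, so a doubtful value has no duplicate to settle it. Someone decides whether to query it. If that decision is taken with the arm known, low gains in one arm can be queried more often than in the other, and the difference in means shifts. In a non-inferiority trial with a margin of 0.5 g/kg/day, a shift toward the reduced dose raises the chance of a false claim of non-inferiority, and a shift the other way costs power. The principal investigator then also takes the decisions of the final analysis.

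**Working it through.** **1. Inputs and the plan's own figure.** Section 2.1.6 gives SD 2.6, margin 0.5, expected difference 0, one-sided alpha 0.05 and power 80%. With its formula and rounded z values, N = (1.64 + 0.84)² × 2 × 2.6² / 0.5² = 332.6. Unrounded z values give 335, as stated. The total of 1,000 means 500 per arm, or 500 × 0.8 = 400 analysed per arm after the plan's 20% dropout.

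**2. Routes from the data to the arm.**

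- *Identifier.* It corresponds to the group (2.2.3), the dispensing provider can read the dose from it (2.3.1 f), and it is on the follow-up sheet. It reveals the arm only to someone who can decode it. If the ID encodes the group, linking a few IDs to their rations would be enough to decode the rest.
- *Ration and consumption.* Chart 2 gives these sachets per week from week 3:

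| Weight (kg) | Standard | Reduced |
|---|---|---|
| 3.0–3.4 | 9 | 7 |
| 3.5–4.9 | 11 | 7 |
| 5.0–6.9 | 14 | 7 |
| 7.0–9.9 | 21 | 14 |
| 10.0–14.9 | 28 | 14 |

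  No band has the same ration in both arms, so weight plus sachet count gives the arm. Section 2.2.4 accepts that parents can work out the dose this way, but does not consider those who check the data. Whether the count reaches the dataset is not stated. The contents listed for the follow-up sheet (2.3.1 f) and for tablet entry (duties of the data entry clerks) do not include it.
- *List copies.* They are kept at the sponsor's headquarters and at the academic partner. Sealed envelopes are mentioned for the lists sent to the nurses, but not for these copies.

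**3. What the two roles do.** They check all data each evening and pass queries to supervisors, who follow up within 24 hours (2.1.3 c). Section 2.3.2 sends feedback through the research manager for correction on site. The principal investigator sets up the correction process, analyses data during the study, and runs the final analysis.

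**4. Scale, under assumed bias only.** With 400 analysed per arm, SE = 2.6 × √(2/400) = 0.184. If the true deficit equals the margin and bias b favours the reduced dose, the one-sided error is Φ(b/SE − 1.645):

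| b (g/kg/day) | One-sided error |
|---|---|
| 0 | 5.0% |
| 0.05 | 8.5% |
| 0.10 | 13.5% |
| 0.20 | 28.9% |

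One way such a bias could arise, again assumed: with 500 per arm, SE = 2.6 × √(2/500) = 0.164. Suppose the lowest 2% of values in the reduced-dose arm alone were replaced by the mean. The mean of the lowest 2% of a normal distribution lies 2.42 SD below centre, so the arm rises by 0.02 × 2.42 × 2.6 = 0.126, and the error is Φ(−1.645 + 0.126/0.164) = 0.19. With 1% replaced the rise is 0.07. The documents give no basis for either percentage.

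**The case against.** A reader might infer that the primary outcome *is* cleaned unblinded, with ration and arm in view and weights overwritten by the principal investigator. The documents do not support that, for these reasons:

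- The recorded and entered fields, where listed, leave out the ration. The table in section 2.3.1 b also holds activities such as consent and randomization, so a mark there does not prove a field in the dataset.
- Section 2.2.2 withholds the sequences from researchers, and section 2.3.1 f keeps the group off the record. The ID may be no more than a list number that only the list holder can decode. Storing a copy at an institution is not the same as access for the people who check the data.
- Those who check raise queries, and corrections are made on site. The clerks keep a logbook of corrections, and 10% of files are entered twice.
- Annex 8 computes weight gain from admission and discharge weights. Both arms receive the same ration in weeks 1–2, so the ration could not reveal the arm when an admission weight is first checked.
- Lock procedures and analysis sets commonly sit in a statistical analysis plan, which is not shown. Running the final analysis does not in itself contradict section 2.2.4.

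All of this stands, and it limits the point to what may happen. It does not remove it. The protocol itself fixes the group-linked identifier, the access rights, the cleaning roles and the analyst, so these are not matters left to a later plan. Withholding the list does not help if the ID or a ration field reveals the arm. Discharge weights are normally recorded after week 3, when the rations differ.

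A separate and more direct conflict with section 2.2.4 is that the nurses' duties include measuring, allocating and distributing by group. It concerns measurement, and resolving it would not blind the data checks or the analysis.

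**Conclusion.** The point holds in a limited form. The protocol claims that researchers are blind and sets up a workflow that does not protect the claim. Weight gain may be queried, cleaned and analysed with the arm known.

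This rests on stated facts: the group-linked identifier, the evening check of all data, sole raw-data access and cleaning by the same two roles, and the principal investigator as final analyst. It also rests on two unknowns: whether the identifier can be decoded by sight, and whether ration or consumption fields enter the dataset.

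No size of bias follows from the documents. The error rates above, including the 19%, describe assumed biases and are not estimates for this trial. They show only that a shift small against the 0.5 margin would matter. The change is worth making because it is cheap and protects the primary outcome.

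**What to change.** 1. In section 2.2.3, use identifiers that carry no group meaning, and keep the ID-to-arm key separate.
2. In sections 2.1.3 c and 2.3.2, keep ration and consumption fields and the key out of every extract that the principal investigator and the research manager use for checking. Let the ACF supervisors check rations on site.
3. In section 2.2.2, state that both list copies are kept sealed.
4. Set outlier and range limits in advance and apply them identically to all records.
5. Lock the database first. Then run the primary analysis on arms coded A/B, still without ration fields. The independent person who generated the list (section 2.2.3) releases the key afterwards.

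The cost is protocol wording, a restricted data view and slightly more data-management work, with no extra staff or visits. If the sponsor does not want this, section 2.2.4 should no longer say that the researchers are blind.

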## **2.3. Data collection, management and analysis**

### **2.3.1. Data collection methods**

#### **a. Data collection technique**

***Quantitative data*** : Anthropometric equipment (scales, measuring rod, tape measure) will be used to take the anthropometric measurements of the children. Children will only be measured once for each parameter (weight, height, PB, etc.) as in current practice.

Clinical data will be collected during an interview with mothers followed by a physical examination at each weekly consultation.

The socio-demographic and economic characteristics of the children and their families will be collected during structured interviews using a questionnaire taken on enrollment in the study.

The questionnaire will be sent in the language of the family caregiver by the existing local IT.

***Qualitative data***: the focus group, in-depth interviews and field observations will be used for the collection of qualitative data.

### b. Data collection plan

| Frequency of data collection                   | Admission | Weekly treatment max 12 weeks | Dump | Monthly follow-up +3 months after discharge | Monthly follow-up at +6 months after discharge |
|------------------------------------------------|-----------|-------------------------------|------|---------------------------------------------|------------------------------------------------|
| Selection for inclusion in the study           | X         |                               |      |                                             |                                                |
| Information, consent and randomization         | X         |                               |      |                                             |                                                |
| Sociodemographic questionnaire                 | X         |                               |      |                                             |                                                |
| Physical examination                           | X         | X                             | X    |                                             |                                                |
| Anthropometric measurements                    | X         | X                             | X    | X                                           | X                                              |
| Distribution of RUTF                           | X         | X                             |      |                                             |                                                |
| Psychomotor Development Score (DPM) Assessment | X         |                               | X    |                                             | X                                              |
| Individual interview for acceptability study   |           |                               |      |                                             |                                                |
| FGD                                            |           |                               |      |                                             |                                                |

### *Staff recruitment and training*

The study should be organized under conditions as close as possible to routine practice. As a result, it is the affected providers (2 per UNTA) in the selected health centers who will collect the main data. The ACF nutrition supervisors will be called upon to supervise the UNTAs and ensure that the strict application of the SAM treatment protocol is observed. The researchers will ensure the training of providers and the quality control of the data for the proper conduct of the study for the data collection phase. Only interviewers for the qualitative part and data entry agents will be recruited.

The investigators must be either anthropologists or health personnel who have already conducted focus groups and in-depth interviews in the past (at least one experience in 2 different studies). Data entry agents must be people with experience in collecting data on tablets (at least 2 different studies).

The teams leading the research, including IT, data entry officers, ACF supervisors, RECOS, sociological investigators, will be trained on the research protocol, taking anthropometric measurements, PCIMA, conducting structured interviews, 'assessment of the psychomotor development of participants and the use of tablets. In addition, training on the quality of the intervention, namely the PCIMA, will be organized by the investigation team. During all the trainings, an emphasis will be placed on practice and a standardization test will be organized (especially for the staff of the CS) to ensure the fidelity and accuracy of the anthropometric data taken by the participants.

The investigators will be trained on facilitating focus groups, in-depth interviews and taking notes.

All the teams (of the qualitative and quantitative part) will be trained on the respect and strict observance of this trial protocol.

The data will be secured every evening on a web server via an internet connection and an additional backup will be made on an external hard drive every Friday evening to serve as a backup in the event of a data crash.

### **c. Study pre-test phase**

Before starting, a pre-test phase will be organized to assess the feasibility of the field study. All questionnaires will be tested before the study and back-translated to verify the correct translation of the words and questions, the newsletter and the consent form.

In each of the two health zones selected, two UNTAs not part of the study will be chosen for the pre-test.

The recruitment criteria will be applied as in the study itself. The agents of the selected UNTAs will be employed for the pre-test.

The pre-test will take place over three days and the teams will be made up of three people from the UNTAs selected for the study. In order not to disrupt the proper functioning of the UNTAs, the agents will take turns participating. Per day, in each team, the three agents will come from the three different UNTAs. The remaining two will cover work in their respective UNTAs.

After the pre-test, the data collected will be analyzed in order to assess the feasibility of the study and the mastery of the tools by the agents. After analysis, recommendations will be possible improvements.

#### **e. Organization of bodies**

The Working Group meets once a week, every Tuesday, to design the study. After the start of the implementation, the meetings will take place once a month for the follow-up, the search for solutions to the encountered challenges, then the cleaning of the data, their analyzes and the writing of the final scientific articles. A Report is produced tracing the exchanges and what is stopped for the protocol.

The Working Group convenes the COPIL for decision-making at the major stages of the research project: 1) validation of the final protocol, including the sub-studies, the budget and the timetable; 2) start of the data collection phase 3) any temporary suspension or modification to protocol or other during the study 4) preliminary results 5) final project report 6) results communication plan.

The WG presents to the COPIL the progress of the project, the decision options and analyzes of these options (consequences, risks, cost), and implements the decisions of the COPIL.

The COPIL or project steering committee is made up of decision-makers from the various project partners:

- **ESP Kinshasa:** Teacher. [name], validating the scientific quality of the project;
- **ACF in DRC:** the Director [name] or his deputy by delegation, validating the mission strategy including operational research, investments in the research project, submission of proposals; the health nutrition RDD validating the technical strategy and the consistency of the research project with it, the resources put into the project (human time);
- **ACF in Paris:** the Regional Director of Operations or her deputy by delegation, validating ACF's humanitarian strategy in general and investments; the head of research at ACF validating scientific partnerships, respect for good research practices and the resources put into the project (human time), the head of the health nutrition sector validating the technical relevance of the research project, its prioritization among 'others in the health nutrition field, the resources put into the project (man time).

